## Abstract

**Background:**

Caring for a person with dementia has profound physical, psychological, social and financial impacts on the carer, while morbidity in carers has detrimental effects on outcomes in people with dementia. A 10-day hospital-based residential carer training program (BMJ 299(6712):1375–1379, 1989) delayed residential care placement, delayed mortality, reduced carer’s psychological morbidity and lowered care costs. This study aims to evaluate the effects of a similar program adapted for use with residential respite.

**Methods/Design:**

This is a single-arm longitudinal study conducted at a residential aged care facility involving 100 people with dementia and their primary carers. In a 7-day residential program, carers will attend intensive training sessions while the people with dementia are engaged in daily activities. Data will be collected at the start of the residential program (baseline), at 6 months (post 1) and at 12 months (post 2) after completion of the program. The primary outcome is carer psychological distress. Secondary outcomes include carer burden, carer quality of life and time to residential care placement.

**Discussion:**

This study will provide evidence on the effectiveness of the program in reducing carer distress and burden as well as delaying institutionalisation of the person with dementia, which may have important implications for policy.

## Background

Approximately 70% of people with dementia in Australia live in the community and most of them receive some informal care (AIHW 2012). Informal carers play a pivotal role in the lives of people with dementia living in the community. They provide assistance with core and non-core activities, either continuously or for more than 40 hours per week (Ory et al. 1999; AIHW 2012). The majority of people with dementia have a ‘profound’ level of disability and this places a high demand on the carer (AIHW 2012). Consequently, dementia carers often experience greater burden than carers of people with other chronic conditions or disabilities (Ory et al. 1999), and the experience of providing care has been described as an ‘unremitting burden’ (Anderson 1987).

Carer burden refers to the carer’s perception of the extent to which their physical, psychological, social and financial status has been affected as a result of care provision (Zarit et al. 1986). High levels of burden have been consistently reported in carers of people with dementia (Schulz et al. 1995; Baumgarten et al. 1992; Haley et al. 1987; Pinquart and Sörensen 2003) and such burden may persist up to two years after the person with dementia’s admission to formal care (Waltrowicz et al. 1996). Longitudinally, depression severity increased in carers who received usual care only while it decreased in those who received additional counselling and support (Mittelman et al. 2008). Mean level of burden and percentage of carers reporting a high level of burden also increased across time (Brodaty et al. 2013). Besides effects on psychological well-being, dementia caregiving also has significant adverse effects on the carer’s physical health (Vitaliano et al. 2003). Carers of people with dementia generally report poorer health (Haley et al. 1987; Baumgarten et al. 1992) and greater use of health services (Haley et al. 1987; Kiecolt-Glaser et al. 1991) than their non-caregiving counterparts.

The level of burden experienced by carers can be influenced by a myriad of factors. Behavioural and psychological symptoms of dementia (BPSD) (e.g., aggression, agitation) have been shown to be associated with carer burden (Black and Almeida 2004; Donaldson et al. 1998). Moreover, carers who reported lower satisfaction with the social support they receive or had greater reactions to the person with dementia’s behavioural problems had more symptoms of depression (Mittelman et al. 2008). The association between severity of the illness (either cognitive or functional impairment) and carer burden, however, was weak (Brodaty and Hadzi-Pavlovic 1990). Carer outcomes may also be influenced by the specific coping strategies used or the level of self-efficacy (Saad et al. 1995; Kneebone and Martin 2003; Fortinsky et al. 2002; Gilliam and Steffen 2006).

Adverse carer outcomes can lead to adverse outcomes in people with dementia. For instance, high levels of carer burden is a consistent significant predictor of institutionalisation (Yaffe et al. 2002; Gaugler et al. 2003; Hébert et al. 2001), and carer psychological morbidity was also a significant predictor of mortality of the care recipient (Brodaty et al. 1993). Therefore, carer interventions may benefit both the carer and the person with dementia. Carer interventions have significant but modest effects in improving carer knowledge, reducing carer burden, reducing psychological morbidity and delaying institutionalisation (Brodaty et al. 2003; Pinquart and Sörensen 2006). There is evidence that these effects can be maintained for up to 11 months post-intervention (Pinquart and Sörensen 2006). In particular, a 10-day Prince Henry Hospital residential carer training program proved effective in delaying residential care placement, delaying mortality, reducing carer’s psychological morbidity and lowering care costs (Brodaty and Gresham 1989; Brodaty and Peters 1991; Brodaty et al. 1993, 1997). These results suggest that carer training provided early in the course of dementia has significant benefits on the outcomes of people with dementia, and therefore such intensive carer training programs should be made more extensively available.

Residential respite care is defined as alternative, short-term care in a residential aged care facility (RACF) with the main purpose of providing the family carer with respite and support. The use of residential respite care has steadily increased in Australia, but take up rates remain low, with only 32% of eligible people with dementia accessing residential respite care services within 12 months of gaining approval (AIHW 2012). There appears to be little empirical support for the efficacy of residential respite care, with some studies even reporting adverse effects on people with dementia, such as an increase in problem behaviours and earlier institutional placement (Brodaty and Gresham 1992). However, anecdotal reports from carers suggest residential respite care may have significant benefits provided carers are well informed and the most appropriate services are utilised. Residential respite care can provide an opportunity to combine existing knowledge about carer interventions with respite.

The principal aim of this study is to evaluate, in an open single-arm trial, the effects of the *Going to Stay at Home* program, which is adapted from the Prince Henry Hospital program for use with residential respite.

It is hypothesised that:carer psychological distress will be reduced at 6- and 12-month follow-up compared to baseline,carer burden will be reduced at 6- and 12-month follow-up compared to baseline,there will be no increase in BPSD in the person with dementia, anda minimum of 60% of carers will have the person with dementia still living at home at 12-month follow-up.

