*Carer burden*: The 12-item Zarit Burden Interview, short version (ZBI-12) (Bédard et al. 2001; Zarit et al. 1980) is a self-report measure of burden experienced in the caring role. The ZBI-12 has been shown to yield results comparable to those of the original full version (Bédard et al. 2001). Higher scores indicate greater burden.*Carer quality of life*: The 13-item Older People’s Quality of Life Questionnaire – Brief (OPQoL-Brief) (Bowling et al. 2013) will be used to measure quality of life. Higher scores indicate better quality of life.*Time to residential care placement*: Time between recruitment and residential care placement of the person with dementia will be measured in days.*Carer functional health status*: The 12-item Short Form Health Survey, version 2 (SF-12v2) (Ware et al. 1996) will be used to assess carers’ functional health status in the physical and mental domains; higher scores indicate better health.*Carer needs*: A 11-item self-report questionnaire (Harrison et al. 2013) covering various areas on which carers for people with dementia may need information will be used to assess the met and unmet needs of the carer.*Resource utilisation*: The Resource Utilization in Dementia – Lite instrument (RUD Lite) (Wimo and Winblad 2003) will be used to assess the utilisation of both formal and informal care and the associated costs. This is administered as an informant-report questionnaire rather than through an informant interview.*Instrumental activities of daily living (IADL)*: The Instrumental Activities of Daily Living Scale (IADL) (Lawton and Brody 1969) will be used to assess people with dementia’s competence in performing eight types of IADL. This will be administered in the form of an informant-report questionnaire.*Activities of daily living (ADL)*: The Physical Self-Maintenance Scale (PSMS) (Lawton and Brody 1969) will be used to assess people with dementia’s competence in six types of behaviours including toileting, feeding, dressing, grooming, physical ambulation and bathing. The version used here separates toileting into two items covering bladder and bowel control. This will be administered as an informant-report questionnaire.*Quality of life*: The proxy version of the 13-item Quality of Life – AD (QoL-AD) (Logsdon et al. 1999, 2002) will be used to assess the quality of life of people with dementia.*Neuropsychiatric symptoms*: The 12-item Neuropsychiatric Inventory (NPI) (Cummings et al. 1994) is an informant-rated measure of the severity and frequency of behavioural and psychiatric disturbances in the people with dementia, collected through an interview with the carer. Higher scores indicate more BPSD.*Agitation*: The 37-item Cohen-Mansfield Agitation Inventory – Community (CMAI-C) (Cohen-Mansfield et al. 1995) is an informant-rated measure of the frequency of agitated behaviours in the people with dementia, collected through an interview with the carer. Higher scores indicate greater agitation.*Dementia severity*: The Global Deterioration Scale (GDS) (Reisberg et al. 1982) will be used to classify people with dementia based on the relative severity of their cognitive impairment and their function in activities of daily living; higher scores indicate more severe dementia. This will be rated by the staff of the respite facility.

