### Statistical analysis

#### Sample size

A target sample size of 100 person with dementia-carer dyads has been estimated to provide over 80% power to detect a moderate effect size (Cohen’s d = 0.3) difference at a significance level of 0.05 (two-sided), assuming a medium within-subject correlation (ρ = 0.5) between pre- and post-intervention measures.

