#### Outcome analyses

The difference in outcome measures before and after intervention will be examined using a paired *t*-test at a significance level of 0.05 (two-sided). To control for covariates (NPI severity, dementia severity) linear mixed models will be used.

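### The hypothesis of no increase in BPSD is paired with tests for a difference and no margin, so short of a significant fall only a non-significant result can favour it

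*Protocol article*

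**What the plan says.** The Background lists four hypotheses. The first two expect reductions in carer distress and carer burden, and the fourth sets a minimum proportion of people still at home at 12 months. The third is of a different kind: "there will be no increase in BPSD in the person with dementia". It names no instrument, no time point and no size of increase that would be tolerated.

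Outcome measures lists two secondary outcomes that bear on it: the NPI ("Higher scores indicate more BPSD") and the CMAI-C ("Higher scores indicate greater agitation").

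Outcome analyses gives one approach for all outcomes: "The difference in outcome measures before and after intervention will be examined using a paired" t-test, two-sided at 0.05. It adds: "To control for covariates (NPI severity, dementia severity) linear mixed models will be used". Neither method comes with a margin or a confidence-bound rule for BPSD.

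Sample size is also built on detecting a difference: "A target sample size of 100 person with dementia-carer dyads has been estimated to provide over 80% power" for a standardised difference of 0.3, "assuming a medium within-subject correlation (ρ = 0.5) between pre- and post-intervention measures".

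**The concern.** A test for a difference suits the first two hypotheses, which predict a change. It does not suit the third. The null of the paired t-test is already no change, so the test can count against the hypothesis (a significant rise) or support it through a significant fall. If BPSD simply stays level, which is what the hypothesis describes, the only result available is a non-significant one, and that does not separate a stable mean from a rise the data were too few or too noisy to show. The mixed models share this limitation.

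The incentive then runs the wrong way. For carer distress and burden, lost or noisy data make the hoped-for conclusion harder to reach. For BPSD, they make a reassuring-looking result more likely.

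This matters because the Background itself notes that some studies of residential respite found more problem behaviours afterwards, and the Discussion expects the findings to bear on policy.

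**Working it through.** **Inputs.** From Sample size: n = 100 pairs, d = 0.3, two-sided alpha 0.05, rho = 0.5. The article gives no SD for the NPI or CMAI-C, so everything is in SD units. Assumed here, because the article gives no figure: true rises of 0.1 and 0.2 SD, and 80 or 60 complete pairs.

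**Step 1: SD of change.** SD_diff = sqrt(2(1 − rho)) = sqrt(2 × 0.5) = 1.0 SD, so a rise of d SD is a paired effect of d.

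**Step 2: reproduce the plan's figure.** Power comes from the non-central t distribution with n − 1 degrees of freedom and non-centrality d × sqrt(n) / SD_diff. For d = 0.3 and n = 100 this is 0.3 × 10 = 3.0, which gives power of 84.4%. The normal approximation, Φ(3.0 − 1.96) = Φ(1.04), gives 85.1%. The stated figure of over 80% is correct; 80% is reached at 90 pairs.

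**Step 3: chance that a true rise gives p > 0.05** (1 − power, same method):

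| True rise | 100 pairs | 80 pairs | 60 pairs |
|---|---|---|---|
| 0.1 SD | 83% | 86% | 88% |
| 0.2 SD | 49% | 58% | 67% |
| 0.3 SD | 16% | 25% | 37% |

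The result depends on rho. For a 0.2 SD rise with 100 pairs, the miss rate is 61% at rho = 0.3 and 27% at rho = 0.7.

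**Step 4: what a non-significant result leaves open.** The 95% CI half-width is t(0.975, n − 1) × SD_diff / sqrt(n): about 0.20 SD with 100 pairs and 0.26 SD with 60. An observed rise just short of significance therefore has an upper limit near 0.20 + 0.20 = 0.40 SD with 100 pairs, or 0.26 + 0.26 = 0.52 SD with 60. Both exceed the 0.3 SD that the trial is sized to detect.

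**Step 5: what a confidence-bound rule would need.** If the claim requires the upper limit of the two-sided 95% CI to lie below a margin m, the power when the true change is zero is that of a one-sided 0.025 paired t-test with non-centrality m × sqrt(n) / SD_diff:

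| Margin m | Pairs for 80% power | Power, 100 pairs | Power, 80 pairs | Power, 60 pairs |
|---|---|---|---|---|
| 0.2 SD | 199 | 51% | 42% | 33% |
| 0.25 SD | 128 | 70% | 60% | 48% |
| 0.3 SD | 90 | 84% | 76% | 63% |
| 0.4 SD | 52 | 98% | 94% | 86% |

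The margins are illustrative, since the article gives none.

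**The case against.** The strongest reply is that the article states no decision rule. It says differences will be examined, not that p > 0.05 confirms anything. That is right. A reader might infer that the plan declares the hypothesis confirmed whenever the test is non-significant, but no sentence says so. What stands is that the article states both the hypothesis and the test, and short of a significant fall the test offers no other route to a favourable reading.

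A second reply concerns power. With 100 complete pairs, a 0.3 SD rise would be detected 84% of the time, so calling the comparison underpowered without qualification would be wrong. The exposure is to smaller rises and to lost pairs. The fourth hypothesis would be met with up to 40% of people no longer at home, but leaving home is not the same as missing an assessment, so 60 pairs remains an assumption.

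Third, one might be tempted to call this the trial's only check on harm to the person with dementia. The documents do not support that. Quality of life, activities of daily living, dementia severity and time to placement are also collected, and the fourth hypothesis addresses earlier placement, the other adverse effect named in the Background. The third hypothesis is the only one about behavioural symptoms.

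Finally, a margin for a secondary outcome could sit in an analysis plan that is not shown. That would excuse silence. It does not remove the mismatch between a hypothesis and a method that are both stated, but it does lower the severity.

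**Conclusion.** The point holds as a mismatch between a stated hypothesis and the stated analyses. Unless BPSD falls significantly, the planned tests can lean towards the hypothesis only through non-significance, and that is weak evidence here: a rise of 0.2 SD would go undetected in about half of trials with all 100 pairs and in about two thirds with 60. At the design effect of 0.3 SD, the miss rate is 16% with 100 pairs and 37% with 60.

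These figures rest on rho = 0.5 applying to the BPSD measures, on an assumed 0.2 SD rise, and on assumed losses. The sample-size statement itself is correct. Severity is moderate: BPSD is secondary to carer distress, and in a single-arm study even a well-supported statement of no increase would describe change from baseline, not an effect of the program.

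**What to change.** Before analysis:

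1. Name one BPSD measure for the hypothesis (for example the NPI total, with the CMAI-C as supportive) and one time point. Two instruments and two follow-ups otherwise leave four possible tests.
2. State the largest mean increase that would be tolerated and justify it on its own merits. A margin of 0.3 SD should not be taken just because it fits the sample size: the Sample size section itself describes that effect as moderate.
3. Report the mean change with its two-sided 95% CI, and claim no increase only if the upper limit lies below that margin.
4. If no margin can be justified, reword the third hypothesis as estimation of the change in BPSD, and state that p > 0.05 will not be reported as showing no increase.

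The cost is wording and the choice of a margin; no new data or participants are needed. The real price is a claim that is harder to make. With no true change, the chance of excluding 0.3 SD is 84% with 100 pairs and 63% with 60; for 0.2 SD it is 51% and 33%. The report should also say that, without a control arm, the result concerns change from baseline only.

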## Methods/Design

### Study design

A single-arm longitudinal design will be used. Data will be collected at three time points: at the start of the residential program (baseline), at 6 months (post 1) and at 12 months (post 2) after completion of the program.

### Setting

The study will be conducted in an eight-bedroom cottage at an RACF in southern Sydney, Australia.

### Recruitment of participants

People with dementia and their primary carers enrolled in the *Going to Stay at Home* program at the RACF will be invited to participate in this evaluation study. Participants of the GTSAH program will be recruited through the community care division of the RACF, aged care assessment teams, carer groups and hospitals, and will then be clustered into groups of four to six person with dementia-carer dyads according to their demographic characteristics.

Inclusion criteria for people with dementia:

confirmed diagnosis of dementialiving at home with a primary carerable to understand and communicate in Englishinformed consent (self and/or proxy) and verbal assent to participate

Exclusion criterion for people with dementia:

no written consent and/or verbal assent to participate

Inclusion criteria for carers:

able to understand and communicate in Englishinformed consent, and where appropriate, consent for the person with dementia to participate

Exclusion criterion for carers:

no written consent to participate

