#### Program for carers

There will be 14 intensive psychoeducation sessions for carers. These sessions will be delivered in an informal structure, with didactic segments, group work, modelling and role play. The sessions cover the following topics:*Combating isolation*. Carers will be encouraged to share their experiences of the caring role to establish an open, supportive relationship among carers.*Medical aspects of dementia*. This session will provide information on the causes of different types of dementia, behavioural and psychiatric changes that may occur, and other common comorbidities including depression and delirium.*Planning for the future*. The need to plan for future emergencies and unforseen events (e.g., unplanned hospitalisation or death of the carer) will be discussed in this session. Other issues such as driving, legal and financial matters, as well as Advance Care Planning will also be explored.*Re-roling*. This session will explore the issues pertaining to the changes in roles and responsibilities between the person with dementia and the carer. Practical problem solving skills will be taught to help carers encourage the person with dementia to allow the carer to take over some of the tasks while maintaining his/her dignity and to develop the carer’s confidence in taking over these roles.*Reminiscence and reality orientation*. Carers will be provided with information on techniques of reminiscence (e.g. use of a life history book), environmental reality orientation (e.g. use of signs or clocks) and validation to enable the person with dementia to maintain connection with their environment as well as improve the communication between the carer and the person with dementia.*Communication*. Information on receptive and expressive dysphasia that the person with dementia may experience and how these may affect communication will be provided, and then carers will have the opportunity to learn communication strategies to enhance understanding.*Assertion*. Carers will be provided with an understanding of assertive, non-assertive and aggressive behaviours, a “carer’s bill of rights” and strategies to cope with criticisms to ensure that they are heard and understood and their personal rights are maintained.*Therapeutic use of activities*. Activities that may be meaningful and enjoyable to the person with dementia will be identified in this session and carers will be provided with knowledge of activity analysis that enables them to break down familiar tasks into component steps and to modify or eliminate steps that prevent the person with dementia from completing them.*Work simplification, organisation and safety in the home*. Problem solving skills of prioritising, simplifying and using outside assistance will be explored to help carers achieve a balance of work, leisure and rest in their daily life. Tools to identify risks within the home environment will be provided and safety measures to minimise the risk to the person with dementia will be discussed.*Nursing skills*. Clinical issues associated with dementia such as incontinence, medication, mobility, personal care and acute illness will be covered and carers will receive hands-on experience in using clinical care equipment that can be used to aid care practices.*Fitness*. Information about the benefits of exercise for both the person with dementia and the carer will be provided, and a daily exercise routine will be established.*Nutrition*. Changes in diet, food intake and nutritional needs of the person with dementia will be examined, and carers will be provided with practical skills to enhance intake as well as improve the eating experience.*Caring for self*. This session will provide carers with the opportunity to identify their need for support and they will be taught a variety of relaxation and stress management techniques.*Using community services*. Information about the types of support services available in the community as well as how to contact and access these services will be provided.

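### The program is delivered in groups of four to six dyads, but the paired t-test and the power calculation treat the 100 dyads as independent; if changes correlate within groups, type I error exceeds 5% and power may fall below 80%

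*Protocol article*

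**What the plan says.** The study has one arm (Study design: "A single-arm longitudinal design will be used"). Under Recruitment of participants, those joining the program "will then be clustered into groups of four to six person with dementia-carer dyads according to their demographic characteristics". Under Program for carers, the teaching is interactive: "These sessions will be delivered in an informal structure, with didactic segments, group work, modelling and role play". Table 1 adds socialising on five evenings, a carers' outing, and a session whose topic the carers choose.

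Under Sample size: "A target sample size of 100 person with dementia-carer dyads has been estimated to provide over 80% power". The target is a "moderate effect size (Cohen’s d = 0.3) difference at a significance level of 0.05 (two-sided". The only other input is the correlation of the two measurements, which the text sets by "assuming a medium within-subject correlation (ρ = 0.5) between pre- and post-intervention measures".

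Under Outcome analyses, the before-after difference "will be examined using a paired *t*-test at a significance level of 0.05 (two-sided". Linear mixed models are mentioned in one further sentence, for covariate control by NPI severity and dementia severity. Neither the sample size text nor the analysis text mentions the program group.

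**The concern.** A one-sample test on change scores takes the variance of the mean change to be the variance of one change divided by 100. That is correct only if the dyads' changes are independent. Here carers are taught, practise and socialise together in small groups, and peer support is one of the aims of the program. Some groups may gel better than others, and content can differ because one session is chosen by the carers. Each of these acts on the change itself. With a single arm there is no comparison group in which such group effects would also appear, so the between-group part of the variance goes straight into the uncertainty of the before-after estimate.

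If changes are positively correlated within groups, the paired t-test gives intervals that are too narrow and p-values that are too small, for the primary outcome and for every secondary change tested in the same way. The planned power is also optimistic once the test is made valid. The estimated mean change itself is not biased by this.

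**Working it through.** **Inputs from the protocol.** n = 100 dyads; d = 0.3; pre-post correlation 0.5; two-sided α = 0.05; group size 4 to 6. If all 100 dyads are analysed, that is 100/6 ≈ 17 to 100/4 = 25 groups; a size of 5 gives 20.

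**Assumed input.** The ICC of the change scores. The protocol gives none, so 0 to 0.10 is shown.

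**Step 1: the plan's own figure.** The standardised mean change is d_z = d / √(2(1 − ρ)) = 0.3 / √(2 × 0.5) = 0.3. The noncentrality is 0.3 × √100 = 3.0. Power from the noncentral t with 99 df is 84.4% (85.1% by the normal approximation), so the claim of more than 80% reproduces. Under independence 90 dyads would give 80%. The stated inputs contain no allowance for clustering; the only slack is the difference between 90 and 100.

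**Step 2: effect of clustering.** With group size m:

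- Design effect: DE = 1 + (m − 1) × ICC
- True α of the paired t-test: 2[1 − Φ(1.96/√DE)]
- Effective n: 100/DE
- Power on effective n: noncentral t with noncentrality 0.3 × √(100/DE) and 100/DE − 1 df
- Power with group-level df: the same noncentrality, but 20 − 1 = 19 df

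Example at m = 5 and ICC = 0.05: DE = 1 + 4 × 0.05 = 1.20; √1.20 = 1.095; 1.96/1.095 = 1.79, so α = 7.4%; effective n = 100/1.20 = 83.3; noncentrality = 0.3 × √83.3 = 2.74.

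Results for m = 5 (20 groups):

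| ICC of change | DE | True α | Effective n | Power, effective n | Power, 19 df |
|---|---|---|---|---|---|
| 0 | 1.00 | 5.0% | 100 | 84.4% | 81.2% |
| 0.01 | 1.04 | 5.5% | 96 | 82.9% | 79.7% |
| 0.02 | 1.08 | 5.9% | 93 | 81.5% | 78.2% |
| 0.05 | 1.20 | 7.4% | 83 | 77.2% | 73.8% |
| 0.10 | 1.40 | 9.8% | 71 | 70.6% | 67.2% |

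Power on effective n crosses 80% at an ICC of about 0.03. With 19 df it crosses at about 0.01.

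**Step 3: check by simulation.** In 100,000 simulated trials per ICC with no true change, using 20 groups of mixed size 4 to 6, the paired t-test rejected in 5.0% (ICC 0), 6.0% (0.02), 7.4% (0.05) and 9.7% (0.10). This agrees with the formula.

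**Step 4: sensitivity to the number analysed per group.** True α by the same formula:

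| m | ICC 0.02 | ICC 0.05 |
|---|---|---|
| 3 | 5.5% | 6.2% |
| 4 | 5.7% | 6.8% |
| 5 | 5.9% | 7.4% |

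With nearly all groups at six dyads, α at ICC 0.05 is 7.9%.

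**The case against.** Several objections carry weight.

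- **No ICC is given.** At ICC 0 the test keeps its 5% level. A reader might infer that the type I error is known to exceed 5%. The protocol does not support that; the inflation depends on a positive correlation of changes.
- **Demographic grouping is weak evidence by itself.** A reader might infer that similar dyads must have correlated changes. Similarity that stays constant over time cancels in a paired difference; only similarity in change matters. The better argument is the shared sessions and peer contact.
- **The exposure is short.** The shared week precedes outcomes collected 6 and 12 months after the program. The protocol does not show how much group correlation would remain by then.
- **Groups in the analysis may be smaller.** Four to six is the size of the program group, whose members are then invited into the evaluation. Refusal and dropout reduce the number analysed per group, and with it the inflation (Step 4).
- **The mixed model might include the group.** The single sentence on linear mixed models gives no random-effects structure, a detail that an article commonly leaves to a fuller document. It cannot be read as excluding a group term, and no fault is found with it here.

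These points limit the size and certainty of the problem. They do not remove it. The paired t-test and the power inputs are stated outright, both assume independence, and the shared delivery that puts this in doubt is described in the same article. Nor does differencing answer the point, because group teaching and peer support act on the change.

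**Conclusion.** The concern holds in conditional form. If changes correlate within program groups, the stated test understates its standard error by a factor of √DE: about 1.04 at ICC 0.02, 1.10 at 0.05 and 1.18 at 0.10 with five dyads per group. The corresponding type I errors are 5.9%, 7.4% and 9.8%.

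A reader might go further and conclude that the planned power is not delivered at all. The figures do not show that: on effective n it is still about 81.5% at ICC 0.02. It may fall below 80%, depending on the ICC and on how degrees of freedom are counted.

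These results rest on an assumed ICC, on about five analysed dyads per group, and on the protocol's own d and ρ. With clusters this small the effect is modest, and it can be corrected at analysis provided that group membership is recorded. It should be fixed, but it does not invalidate the study.

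**What to change.** 1. Record a program-group identifier for every dyad.
2. Replace the unclustered paired t-test, for the primary and secondary before-after changes, with an analysis that allows for the group. Either a mixed model with a random group effect on the change (group by time) or group-clustered standard errors would serve. Use a small-sample correction, since there will be only about 20 groups.
3. Restate power for the existing target of 100 dyads with DE = 1 + (m − 1) × ICC over a stated range of assumed ICCs, and say whether group-level degrees of freedom are used.

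The cost is one identifier, one model term and a revised power statement, with no new outcome data and no additional dyads. Intervals become slightly wider and the power figure slightly less favourable. Even if the ICC proves to be zero, the price in power is only the loss of degrees of freedom, from 84.4% to about 81.2%.
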